### Patient eligibility criteria

To be eligible to participate patients must...

#### Inclusion criteria

- be aged 18 years or older
- be diagnosed with HIV-1 infection
- be treated with a combination antiretroviral therapy (composed of 2 to 3 different drugs)
- have had known or suspected adherence problems in the past 12 months based on a detectable viral load test result per local standards, patient report, and/or report by the healthcare team (by the physician, nurse, social worker or pharmacist)
- be treated for HIV at the Chronic Viral Illness Service of the McGill University Health Centre
- be able to speak and understand either French or English
- possess a smartphone with an appropriate data plan and/or home Wi-Fi connection

- be willing to download the smartphone app

Patients many not participate if they...

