## Aim and objectives

With the present mixed method pilot study, drawing on implementation science, the aim is to develop the methods and tools necessary to undertake a more robust evaluation of the implementation and effectiveness of the I-Score ePROM-within-Opal innovation (henceforth, the I-Score intervention) in routine HIV care with individuals on ART. This study's primary objectives are to evaluate perceptions of the I-Score innovation (Objective 1) and evaluate the implementation strategy (Objective 2) in terms of recommended implementation science metrics for patient-reported outcome measure initiatives in routine care (Stover et al., 2020). Its secondary objective (Objective 3) is to determine if the intervention shows promise and the chosen outcomes are useful, by observing collected data on select effectiveness outcomes (patient and service outcomes).

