## Methods

### Study design

This 6-month pilot study will adopt a one-arm mixed method type 3 implementation-effectiveness hybrid design and be conducted in a single clinical site (see Figure 3). Type 3 hybrid designs emphasize testing the implementation strategy of an evidence-based intervention, but merely observing data collected on intervention effectiveness (Curran et al., 2012). While syntheses of effectiveness evidence for PROM use in routine care have typically found mixed results, with inconsistent impacts on patient outcomes (e.g., Boyce et al., 2013, Valderas et al., 2008), a more recent systematic review finds the evidence supports PROM use in standard care, particularly to improve patient-provider communication and decision-making in clinical practice (Isaque et al., 2019). The hybrid design also seems justified, given international momentum for PROM use (Rutherford et al., 2020), which may build with the COVID-19 pandemic. Indeed, there are calls for a scale up of electronic PROMs implementation in this crisis for the remote follow-up of chronic conditions, in part, to better screen patients and promptly manage their needs (Marandino et al., 2020).

Mixed methods were adopted in this study as multiple methods are recommended for studying intervention implementation and its problems in complex systems, like HIV clinics (Peters et al., 2013). Regarding the integration of the quantitative and qualitative data collected, this will occur toward study end within a convergent parallel design (Creswell and Plano Clark, 2011). Those directly involved in the analyses will decide upon the specifications of integration. Reporting of this study will seek to satisfy the standards of Good Reporting of a

Mixed Methods Study (O’Cathain et al., 2008) and the Standards for Reporting Implementation Studies (Pinnock et al. 2017).

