### Setting and participants

The study setting is a large hospital-based clinic in Montreal, Quebec, Canada. This clinic, the Chronic Viral Illness Service (CVIS) of the MUHC, offers multidisciplinary care to approximately 2000 adults living with HIV. Five physicians treating individuals with HIV at the CVIS will be recruited to participate as well as 30 of their adult patients. This sample size amply meets rule of thumb recommendations for one-arm pilot studies (Sim & Lewis, 2011). Patients must be confirmed HIV-positive, have a history of known or suspected adherence problems in the past year, be aged at least 18 years old, be on or beginning combination ART, be literate in English or French, and own a smartphone. Full details on eligibility are presented in the next section. Ten female patients will be recruited, to ensure sufficient representation of women living with HIV (Public Health Agency of Canada, 2018).

[figure not shown]

Figure 3. Pilot study design.

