
### *Data collection*

#### *Quantitative component*

The quantitative component will have three sources of data: 1) participant self-report; 2) electronic medical records; and 3) passive data (e.g., on app use to assess fidelity). At T1, T2 (3 months) and T3 (6 months), a study questionnaire will be administered to participants online or, if needed, with a hardcopy, especially to assess implementation outcomes.

At T1, the questionnaire will also ask about socio-demographics (e.g., year of birth, preferred language, sex, sexual orientation, ethnic group identity, immigration, education, income) and digital technology use as well as pose general health questions for patients (year of diagnosis with HIV, treatment satisfaction) and clinical practice questions for physicians (years practicing in HIV, current number of HIV patients). The measures of digital technology use are as follows: frequency of mobile device use (adapted from Schnall et al., 2018), having a health app on one's mobile device (Mahmood et al., 2019), extent of health app use (adapted from Balapour et al., 2019), confidence in reporting medical information using mobile technology (Balapour et al., 2019), and intention to report personal health data with a mobile device app, if asked by a provider (Balapour et al., 2019). All of this information will help contextualize the findings and describe the sample (see the Appendix for the patient and physician questionnaires). Clinical data, namely, HIV viral load in copies/mL, to determine viral suppression, will be extracted from patients' medical health record at the clinic, at T1 and T3.

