Regarding the patient outcomes of Objective 3, barriers to adherence and adherence will be summarized with the minimum, the maximum, the mean, and the standard deviation. Viral load will be reported by absolute and relative frequencies, as it is considered a dichotomous variable. For the service outcome obtained from the physician checklist, we will report the proportion of clinic visits when physicians took action based on the I-Score results, among the visits where an adherence barrier of concern was identified by physicians. Proportions will be reported for T1, T2 and T3 and globally, across time periods. To evaluate evidence of a statistically significant difference in our chosen effectiveness outcomes, we will run a Student's paired t-test for barriers to adherence and adherence and a McNemar test for viral load, between T1 and T3. To complete the analysis of the service outcome, we will use a logistic regression model, considering only the visits where an adherence barrier of concern was identified by physicians. The dependent variable is the binary variable of whether or not an action was taken by physicians and the independent variable is the time, considered as a factor with three independent levels (T1, T2 and T3). We will test the null hypothesis that time has no effect on the probability of taking action, with a t-test on the regression coefficient. We will conclude the analysis by testing the null hypothesis of equality of proportions between all pairwise combinations of time points, with a Student's t-test between two proportions, performing a Bonferroni correction for multiple tests. For all analyses, a significance level of 5% will be adopted.

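### Objective 3 counts p ≤ 0.05 on an uncontrolled T1–T3 change as success in patients chosen for recent adherence problems, so unaided recovery can contribute to or produce that success

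*Protocol*

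**What the plan says.** The inclusion criteria require that patients "have had known or suspected adherence problems in the past 12 months based on a detectable viral load test result per local standards", or on report by the patient or the healthcare team. The Setting and participants section also admits patients who may "be on or beginning combination ART".

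The study "will adopt a one-arm mixed method type 3 implementation-effectiveness hybrid design", with questionnaires at T1, T2 and T3. Viral load "will be extracted from patients' medical health record at the clinic, at T1 and T3". The Objective 3 section takes the latest result on file at each of those times, and no rule distinguishes the T1 value from the test that made the patient eligible.

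Objective 3 is secondary and is meant to "determine if the intervention shows promise and the chosen outcomes are useful". The Quantitative analysis section plans paired t-tests for barriers and adherence and a McNemar test for viral load, T1 against T3, at the 5% level: "To evaluate evidence of a statistically significant difference in our chosen effectiveness outcomes". Table 3 (cited in the text as Table 2) lists p ≤ 0.05 as the success threshold for each Objective 3 outcome, without a direction, an effect size or a comparator. Study metrics and instruments adds that missing a set threshold means changes are needed before a definitive trial.

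**The concern.** Adherence and viral load vary over time. Patients picked because of a recent problem, which they or the care team already know about, may improve over six months whatever the I-Score does. Someone just starting treatment would be expected to improve on viral load in any case. With one arm and no measurement before T1, the planned tests cannot tell this from an intervention effect, and the bias runs towards apparent benefit.

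One-arm pilots share this limit. Here it matters more because the Protocol attaches a success rule to the test. The Study design section says that effectiveness data are only observed in this type of hybrid, yet Table 3 turns them into pass or fail by p-value. At stake is a statement about promise that recovery alone could generate.

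**Working it through.** **Inputs from the Protocol.** 30 patients; 80% retention benchmark, so 0.80 × 30 = 24 pairs; 5% level (two-sided assumed, since sidedness is not stated, which puts the nominal chance of a significant improvement at 2.5%); T1–T3 paired t-test and McNemar test; selection window of 12 months. There is no planning figure to reproduce: the sample size rests on a rule of thumb ("This sample size amply meets rule of thumb recommendations for one-arm pilot studies"), with no effect size, SD or power. Correlations, cut-offs and transition rates below are assumptions.

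**1. Change needed to pass.** For the paired t-test, mean change in SDs of the differences = t(0.975, n−1)/√n.
- n = 30: 2.045/5.477 = 0.37
- n = 24: 2.069/4.899 = 0.42

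For McNemar with x patients becoming undetectable and none reversing, exact p = 2 × 0.5^x. x = 5 gives 0.0625 and x = 6 gives 0.031. Without correction, chi-square = x on 1 df, so x = 4 gives p = 0.046.

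**2. Expected drift with no effect.** If patients are the worst part of the distribution on a selection measure S, in SD units, then the drift T1 to T3 = (r(S,T1) − r(S,T3)) × |mean of S among those selected|. For the worst 20% that mean is 1.40.

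| r(S,T1) / r(S,T3) | Drift, worst 20% | Chance of significant improvement, n = 30, worst 20–50% selected |
|---|---|---|
| about 1 / 0.6 | 0.4 × 1.40 = 0.56 | 52–95% |
| 0.8 / 0.5 | 0.3 × 1.40 = 0.42 | 31–73% |
| 0.7 / 0.6 or 0.6 / 0.5 | 0.1 × 1.40 = 0.14 | 7–16% |
| equal | 0 | 2.5% |

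Drift exists only so far as the selecting event is tied more closely to T1 than to T3.

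**3. The Protocol's 12-month rule.** Quarterly values were simulated at −12, −9, −6, −3, 0 (T1), 3 and 6 (T3) months with no effect. A patient is selected if any of the four pre-T1 values falls below a cut-off.
- *Model A, no stable patient differences:* AR(1), 3-month autocorrelation 0.5–0.8, cut-offs −1.28 to −0.5 SD. Mean rise 0.13–0.33 SD; significant improvement in about 8–53% of trials of 30.
- *Model B, stable patient differences of 40% or 60% of variance:* residual autocorrelation 0.3–0.5, same outer cut-offs. Mean rise about 0.03–0.15 SD; significant improvement in about 4–13%.

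For the dichotomised value, the exact McNemar test was significant for improvement in about 1–3% of trials under B and up to about 10% under A. The uncorrected test gave 5–17% under A. The Protocol does not say which version it means.

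**4. Timing.** If every qualifying event is placed exactly 3 months before T1, the t-test figures become 49–94% (A) and 12–62% (B). This is a limiting case, not the Protocol's rule.

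**5. Baseline as qualifying test.** If the latest viral load at T1 is itself the detectable result that qualified the patient, many patients may start as detectable. With 20–50% detectable at T1, 50% of those suppressing unaided and 5% of the others rebounding, exact McNemar shows significant improvement in 3–57% of trials of 30. With 10% detectable it is 0.1%.

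**The case against.** The strongest reply is that this is a declared one-arm pilot. Effectiveness is secondary, the primary outcome is acceptability, and the analysis section ties its score targets for proceeding to a definitive trial to Objectives 1 and 2. That is right, and it limits the weight of the point. It does not remove the Objective 3 thresholds in Table 3, which go further than observing.

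The second reply is that the size depends on the model. This stands. With stable differences between patients, which is plausible given the range of social, material and health-service barriers described in the Introduction, the inflation is slight at the low end. Selection is also looser than a measured low point: suspected problems on report are enough, and neither the I-Score nor the self-rating item is used to select.

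Third, earlier viral loads do not cleanly isolate drift, because patients were selected within that same window, and they serve only one of the three outcomes. This also stands, so they can only be exploratory.

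Stronger readings are tempting. A reader might infer that an ineffective intervention would probably succeed, as the 49–94% figures suggest. Those need every qualifying problem to lie exactly 3 months before T1, while the Protocol allows 12 months. A reader might also infer that the T1–T3 change will set the definitive trial's effect size. No section says so; the Protocol says only that the study will yield data useful for designing that trial.

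**Conclusion.** The point holds for barriers, adherence and viral load. Selection on recent problems, a single arm, a T1–T3 self-comparison and a p ≤ 0.05 success threshold are all fixed in the Protocol, and together they allow recovery or regression to the mean to contribute to or produce success with no I-Score effect. It does not extend to patient management, which is analysed across visits and is not a patient's comparison with themselves.

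The size cannot be derived from the Protocol. Under the 12-month rule the assumed models span about 4–13% to about 8–53% for a continuous outcome, against 2.5%, and about 1–10% for exact McNemar. It is larger if qualifying problems cluster near T1 or if the T1 viral load is the qualifying test, and absent if selection is equally related to T1 and T3. The fault lies in the success threshold and in the lack of any stated caveat, not in choosing a one-arm pilot. It is worth correcting but does not threaten the primary outcome.

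**What to change.** - **Table 3:** remove p ≤ 0.05 as the success threshold for barriers, adherence and viral load.
- **Quantitative analysis, Objective 3 paragraph:** report T1–T3 changes as estimates with 95% confidence intervals (for viral load, the paired difference in the proportion detectable) and label them uncontrolled. State that they will not by themselves establish promise or set the definitive trial's effect size. The wording is needed because an interval that excludes zero carries the same bias as a small p-value.
- **Quantitative component and the Objective 3 section:** from the same record, also extract the dated viral loads from the 12 months before T1 and, where known, the date and type of the qualifying problem. Flag patients whose T1 value is the qualifying test. Show the course before T1 as exploratory context only.

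The cost is a little extra chart extraction and a more modest Objective 3 claim. No visits, tests or patients are added. Some suspected problems will have no date, and barriers and self-rated adherence will still have no values before T1.

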### *Exclusion criteria*

- are participating in a clinical trial at the time of enrollment in this study
- have a cognitive impairment or medical instability that prevents them from participating in the interview
- have insufficient mastery of French or English to participate in the interview and complete the questionnaires
- have insufficient ability to use the app with the technical support provided
- are co-infected with hepatitis C and are being treated for it or have completed treatment 3 months or less ago
- are co-infected with hepatitis B and are either not treated for it or are being treated for it with a medication other than their anti-HIV medication

### *Recruitment and consent process*

Physicians treating patients with HIV at the CVIS will be asked individually to participate, by oral or email invitation (see the Appendix for the email invitation). Patients of participating physicians will be recruited and consented in two ways: 1) when they visit the clinic; or 2) prior to an upcoming clinic visit. When they visit the clinic to meet with a health or social service provider (e.g., physician, nurse, social worker, psychologist), the provider will briefly describe the study. Alternatively, patients with upcoming visits will be identified and contacted to inform them of the study. If the individual agrees, the study coordinator will present the project in greater detail to them in person or over the phone, check the eligibility criteria, and obtain consent. Then, an appointment for a teleconference (on Zoom) will be made with the participant prior to their next regular clinic appointment with their physician to deliver training to use the app and complete the I-Score. Given efforts to limit in-hospital visits and risks for patients during the COVID-19 pandemic, in-clinic appointments with research staff will be avoided, when possible.

### *The I-Score intervention*

During the study, participating patients will visit with their HIV physician three times, at Time 1 (T1), month 3 (T2), and month 6 (T3), prior to which they will complete the I-Score, as instructed. This visit schedule was selected as it fits within guidelines for the clinical follow-up of HIV in Quebec (Ministère de la santé et des services sociaux, 2019), while maximizing the collection of repeated study measurements. Given COVID-19, one visit (T2) will be done remotely (by phone or teleconferencing), while the other visits will be held at the CVIS. The I-Score PROM contains 20 items, covering 6 domains of barriers to ART adherence. Respondents indicate how often each barrier made adherence difficult in the past 4 weeks, with a continuous scale, from never to always. [Additional details on measure scoring and interpretation will be provided to the REB as they become available]. For details on the measure's development see Engler et al., 2018, Engler et al., 2019, Lessard et al., 2019, Toupin et al., 2018.

The core intervention of this pilot consists of having individuals with HIV on ART register on the Opal app and complete the I-Score PROM prior to each of three consecutive visits with their HIV physician. The patients will receive a reminder to complete the I-Score one week before their visit and they will have immediate access to their results. The HIV physician will acquire the I-Score results before each visit via the ORMS dashboard, an appointment and questionnaire management tool integrated with Opal and designed specifically for healthcare providers. The option of graphically presenting scores over time will also be available, allowing physicians and patients to compare past and present scores. It is expected that patients and physicians will review the I-Score results so they can be considered during the clinic visit (see Figure 1).

### *Privacy and security*

The technical cybersecurity aspects of the Opal app conform to the security and governance recommendations for

the development of a patient portal, as identified by the MUHC's Security and Governance team, to ensure the confidentiality of patient data (for details, see the multimedia appendix 2 of Kildea et al., 2019).

### *The implementation strategy*

The multilevel ePROM implementation strategy (Curran et al., 2012), designed for this study, addresses known facilitators and barriers to implementing ePROMs in routine clinical practice (Foster et al., 2018) and draws on recognized implementation strategies (Powell et al., 2012, 2015). Table 1 presents the correspondence between the facilitators and barriers targeted, the chosen implementation strategies to address them, and their relationship to components of the implementation framework used in this study, the CFIR. We will conduct an *Educational meeting* by teleconference with providers and other organizational stakeholders to formally teach them about the intervention and its rationale and respond to concerns. We will provide *Training and consultation* on the ePROM and app by hiring an *Application Manager* (AM). The AM will be available to patients and providers on an ongoing basis, as needed, preferentially by phone or teleconference. They will also help monitor the quality of PROM data. Appointing such a coordinator (or Quality Assurance officer) is a recommended strategy to minimize the impact of missing PROM data (Mercieca-Bebber et al., 2016). The AM will thus oversee the completeness of ePROM data collected and manage any system or software problems, which are potential disadvantages of computer or web-based PROM administration (ISOQOL, 2011). Hence, overall, they will facilitate PROM implementation. Another strategy aims to meaningfully *Involve patients and providers* in the I-Score's implementation. Individuals from both groups will provide input on the proposed study prior to its conduct. Following the I-Score administrations at T2 and T3, physicians will participate in a focus group (by teleconference), while a short semi-structured interview will be conducted with each patient (by telephone or teleconference). Throughout the study, the AM will take field notes on the problems encountered by participants and this feedback will enable *Cyclical small tests of change* to improve implementation, using an evaluation approach guided by the CFIR (Consolidated Framework for Implementation Research) (Keith et al., 2017). This way, we will *Promote adaptability* of the I-Score process, to enable adjustments to local considerations while maintaining the intervention's core components (i.e. I-Score completion by the patient via Opal prior to the clinic visit, review of scores by the physician in conjunction with the visit). Many peripheral components will be adaptable, such as the timing and number of reminders to complete the I-Score and how I-Score results are presented to providers on the ORMS dashboard.
